#### Secondary efficacy outcomes

3.11.2

Secondary outcomes and their definitions are shown in Table 1 and include treatment completion [47] (yes/no), rate of missed appointments [47], and material financial hardship [34] within 6 months post randomization, as well as changes in patient-reported financial worry [31,32], health insurance literacy [43], QOL [35], subjective sleep quality [37] between baseline and 3- and 6-months. A sleep quality parameters will be calculated using the Action-W program and include: sleep duration (total nighttime sleep minutes), sleep efficiency (ratio of nighttime sleep duration to total sleep period), sleep latency (minutes to first sleep epoch), and sleep fragmentation (ratio of number of nighttime awakenings to nighttime sleep duration ∗ 100). The index of sleep fragmentation considers movements of varying intensity [43].

**Table 1 tbl1:** Preliminary Efficacy Outcome Measures and co-variates.

Outcome	Definition	Source
Cost-related cancer care nonadherence *(****Primary)***	Any incidence during the 6 months (measured at 3, and 6 months) when a patient self-reports a positive response to any of: (1) delay, (2) forego, (3) stop, or (4) change in cancer prescribed medication due to cost, (5) refuse recommended cancer tests, or (6) skip cancer office visits due to cost (adapted from Medical Expenditure Panel Survey) [34]. The outcome will be binary (yes/no).	Patient surveys at 3& 6 months. Outcome will also be measured at baseline to control baseline data.
Treatment completion	Receipt of the prescribed cycle of chemotherapy and/or radiation therapy due within the 6-month study period, determined by EMR abstraction (Yes/No) [47]. Patients with treatment interruptions/stoppages because of toxicities, other medical reasons, facility factors, or death will be considered as having completed treatment if they complete all recommended treatment within the 6-month interval. Treatment interruptions/stoppages without medical reasons will be considered incomplete treatment.	EMR
Missed appointment	Proportion of outpatient medical or radiation oncology treatment appointments (including infusion) or office visits (including tele medicine) that is marked as cancellation or no shows and are provider-initiated or are not due to scheduling errors [47]	EMR
Material financial hardship	Any incidence during the 6 months (measured at 3, and 6, months) when a patient self-reports a positive response to any of the following: (1) home sale, refinance or move to affordable rental, (2) loans, (3) reaching credit limits, and (4) bankruptcy) because of your cancer care, or its treatment (adapted from Medical Expenditure Panel Survey) [34]. The outcome will be binary (yes/no).	Patient surveys at 3& 6 months. Outcome will also be measured at baseline to control baseline data.
Financial worry	11-item Comprehensive Score for Financial Toxicity (COST) [31,32]. (Score 0-44; higher score = lower financial worry)	Patient surveys at 3& 6 months. Outcome will also be measured at baseline to control baseline data.
Health Insurance literacy	21-item Health Insurance Literacy Measure [43]. (score 21-84); higher score = higher health insurance literacy)	
QOL	10-item Patient-Reported Outcomes Measurement Information System (PROMIS)-10 version 1.2 [35]. (Score 0-100; higher score = higher quality of life)	
Patient-reported sleep quality	Insomnia Severity Index (ISI). 7-item that evaluates perceived severity of insomnia symptoms [37]. (score 0-28). Score of 10 = clinically significant insomnia	
Total sleep time	The total duration of sleep episodes, calculated from the time the individual falls asleep to the time they wake up [53]	Sleep actigraph
Sleep efficiency	The percentage of time spent asleep while in bed, calculated as (Total Sleep Time/Time in Bed) ∗ 100 [53]	Sleep actigraph
Nighttime awakening	The number of times the individual wakes up during the night [53]	Sleep actigraph
Sleep latency	The time it takes to fall asleep after getting into bed, measured as the time difference between bedtime and sleep onset [53]	Sleep actigraph

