#### Power calculation and sample size

3.12.1

This is a 3-arm pilot randomized controlled trial to gather preliminary data to plan for a large future trial. A sample size of 90 patients (30 patients in each arm) is feasible given the limits of the study timeline and will allow us to characterize key patient variables.

Power analysis was performed to estimate a one-sided 85%, 90% and 95% upper-limit confidence intervals for proportion of patient-reported cost-related cancer care nonadherence at 6 months post-randomization in an experimental arm via the Exact (Clopper-Pearson) formula when the evaluable sample size for a study arm is 30 (Table 2). With an evaluable sample size of 30 in an experimental arm and the anticipated proportion is 0.05, the estimated 95% upper-limit confidence limit is 0.17.

**Table 2 tbl2:** Estimation of one-sided upper-limit confidence interval for primary outcome via the Clopper-Pearson Exact method when the evaluable sample size of 30 in an experimental arm.

The proportion of patient-reported cost-related cancer care nonadherence at 6 months post-randomization in an experimental arm (P)	One-sided upper limit of a confidence interval via the Clopper-Pearson Exact method		
	85%	90%	95%
0.05	0.1296	0.14613	0.17251
0.1	0.19052	0.2093	0.2386
0.15	0.24806	0.26832	0.29948

SPIRIT 2025 checklist of items to address in a randomized trial protocol^a^			
Section/Topic	No	SPIRIT 2025 checklist item description	Reported on page no.

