#### Analysis plan

3.12.3

We will report proposed outcome measures using descriptive measures. A difference and its 95% confidence interval in an outcome endpoint will be estimated via conducting pairwise comparisons between each intervention arm (***CostCOM*** or ***FinEd***) versus ***EUC*** arm. The Exact (Clopper-Pearson) method will be utilized to obtain a 95% confidence interval. Logistic regressions will be used to evaluate the impact of potential co-variates on primary endpoint among study arms. Linear regression analysis will be utilized to model a continuous outcome. For the longitudinal outcomes, we will implement the Generalized Estimating Equations (GEE) approach to adjust for the systematically different observation periods, in which time will be modeled as a fixed effect at each step**.**

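### The missed-appointment definition in Table 1, read as written, counts clinic-initiated cancellations as missed visits; a negation appears to have been lost

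*Protocol article*

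**What the plan says.** Missed appointments are a secondary efficacy outcome taken from the EMR. The text of section 3.11.2 only names it: "rate of missed appointments [47], and material financial hardship [34] within 6 months post randomization". The abstract and section 2 (Objectives) also name it without defining it. The sole definition is in Table 1.

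- Base: "Proportion of outpatient medical or radiation oncology treatment appointments (including infusion) or office visits (including tele medicine").
- Condition for counting as missed: "that is marked as cancellation or no shows and are provider-initiated or are not due to scheduling errors".

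The neighbouring EMR outcome in the same table, treatment completion, treats non-patient causes separately: "Patients with treatment interruptions/stoppages because of toxicities, other medical reasons, facility factors, or death will be considered as having completed treatment", on condition that all recommended treatment is completed within the six-month interval. Stoppages without a medical reason count as incomplete.

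Section 3.12.3 (Analysis plan) sets the scale of comparison with EUC: "A difference and its 95% confidence interval in an outcome endpoint will be estimated via conducting pairwise comparisons between each intervention arm". Logistic regression is named there for the primary endpoint only.

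**The concern.** The condition joins two limbs with *or*. The second limb carries a *not*; the first does not. An outcome labelled missed appointments, in a trial of financial education and navigation, is naturally understood as care that the patient did not attend. There is little reason to name provider-initiated events in such a clause except to exclude them, yet as written they are included.

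This is a stated counting rule, not a detail left to another document. An abstractor who followed it would count clinic cancellations as missed visits in all three arms. The pilot is meant to supply planning data for a larger trial, so an inflated and noisier missed-visit proportion could be carried into that trial's assumptions.

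**Working it through.** **The plan's own figure.** The article's only precision calculation is Table 2 in section 3.12.1: "the estimated 95% upper-limit confidence limit is 0.17", for 30 evaluable patients and a proportion of 0.05. The one-sided Clopper-Pearson upper limit is the 0.95 quantile of Beta(np + 1, n − np) = Beta(2.5, 28.5) = 0.17251, as printed. All nine cells of Table 2 reproduce. The table concerns the primary outcome and does not bear on this point.

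**Logic of the definition.** Let A = provider-initiated and B = due to a scheduling error. Among visits marked as cancelled or no-show:

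| Event | As written: A or not B | Apparent intent: not A and not B |
|---|---|---|
| Not A, not B | counted | counted |
| A, not B | counted | excluded |
| A, B | counted | excluded |
| Not A, B | excluded | excluded |

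The two rules differ on every provider-initiated event. Adding a *not* to the first limb while keeping *or* would not repair it: *not A or not B* excludes only events that are both. The conjunction has to change as well.

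**Effect on the planned contrast.** The article gives no rates, so the following are assumptions. Let p be the patient-attributable missed proportion, 0.20 in EUC and 0.10 in an intervention arm, and let q be the share of visits cancelled by the provider, equal in both arms.

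- Additive: observed = p + q.
- Displacing (a visit cancelled by the clinic can no longer be missed by the patient): observed = q + (1 − q)p, so the difference is (1 − q) × 0.10.

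| q | Additive: EUC, intervention | Difference | Displacing: EUC, intervention | Difference |
|---|---|---|---|---|
| 0 | 0.20, 0.10 | 0.10 | 0.20, 0.10 | 0.10 |
| 0.05 | 0.25, 0.15 | 0.10 | 0.24, 0.145 | 0.095 |
| 0.10 | 0.30, 0.20 | 0.10 | 0.28, 0.19 | 0.09 |
| 0.20 | 0.40, 0.30 | 0.10 | 0.36, 0.28 | 0.08 |

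Lower rates show the same additive result. With 0.08 versus 0.04, adding q = 0.05 gives 0.13 − 0.09 = 0.04, and adding q = 0.10 gives 0.18 − 0.14 = 0.04.

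**Role of the denominator.** In the displacing case, take q = 0.10 and correct the numerator but leave provider-cancelled visits in the denominator. The proportions are 0.9 × 0.20 = 0.18 and 0.9 × 0.10 = 0.09, so the difference is still 0.09. It returns to 0.10 only if those visits leave the denominator too. The reworded definition therefore has to say which is meant.

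**Effect on precision.** Assume a patient-level SD of 0.15 for the patient-attributable proportion, an independent provider-initiated component with SD s, 30 patients per arm and a true difference of 0.10. Then SD = √(0.15² + s²). The 95% half-width is 1.96 × SD × √(2/30), and power is the two-sided 5% normal approximation.

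| s | SD | Half-width | Power |
|---|---|---|---|
| 0 | 0.150 | 0.076 | 0.73 |
| 0.05 | 0.158 | 0.080 | 0.69 |
| 0.08 | 0.170 | 0.086 | 0.62 |
| 0.12 | 0.192 | 0.097 | 0.52 |
| 0.15 | 0.212 | 0.107 | 0.45 |

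The direction is general under independence; the sizes depend wholly on the assumed SDs.

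**The case against.** The strongest reply is that this is a slip of wording in a condensed article. The abstraction form and the full protocol are not shown, the definition is attributed to a cited source, and the coordinators may already work from a correct rule. The treatment-completion row shows that the authors were alert to non-patient causes. This stands in part: the documents do not show that any record has been or will be mis-scored. It does not rescue the sentence, which is the article's only definition and states the rule the wrong way round.

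A reader might also infer that counting provider cancellations dilutes any treatment effect. On a ratio scale it would: 0.09/0.13 = 0.69 and 0.14/0.18 = 0.78, against 0.04/0.08 = 0.50. But section 3.12.3 plans differences, and no ratio is specified for this outcome. On the difference scale the same figures stay at 0.04 throughout. General dilution is therefore not supported. What remains is the mislabelled outcome, the inflated level, the added variance and a possible modest shrinkage of the difference.

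Finally, that the interventions cannot affect clinic-initiated cancellations is a reasonable assumption, but the article does not state it. If provider cancellations differed by arm, the difference could move in either direction.

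**Conclusion.** The definition is wrong as written and should be corrected. Followed literally, it places every provider-initiated cancellation in the numerator, raises the missed-visit proportion in all arms and adds variance. The planned difference is unchanged if these events are purely additive and unrelated to arm. If they displace visits that could have been missed, it shrinks by the fraction q, which is 5% to 20% over the assumed range. The actual size cannot be computed from the documents.

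Severity is moderate. A reader might take the error as a threat to the trial's main result, but the primary outcome is patient-reported cost-related nonadherence, which does not use this definition. The sample size also stands apart from it: "A sample size of 90 patients (30 patients in each arm) is feasible" rests on feasibility, with precision shown for the primary outcome only.

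**What to change.** Reword the numerator in Table 1 to: *marked as cancellation or no-show, excluding those that are provider-initiated or due to scheduling errors*. State whether the excluded visits stay in the denominator; either choice can be defended, but it should be fixed before analysis. Check that the EMR abstraction form carries the same rule.

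The cost is one line in Table 1, one line on the form and, only if records have been abstracted under the literal wording, a re-check of those records. No change to sample size, randomization, surveys or the primary analysis is needed.

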**Co-Variates**		
Sociodemographic	Age, sex, race, ethnicity, marital status, education, employment status, annual household income, address and zip codes (to calculate area deprivation index [54])	Patient survey & EMR at baseline and updated at 3, and 6 months
Insurance	Insurance type	
Health Literacy	Single item Health Literacy [48] (score 1-5; higher score = higher health literacy)	Survey
Use of supportive services	Receipt of out-of-pocket cost communication, financial counseling or assistance as part of usual care	Survey
Comorbidities	NCI morbidity index [39]	Survey
Cancer variables	Type, stage, treatment	
Medical history	ECOG performance status (0, 1 & 2)	

#### Co-variates

3.11.3

We will collect variables such as patient sociodemographic and insurance via surveys and EMR data. Surveys will also include questions to assess health literacy [48], use of supportive services, and comorbidities. Cancer type, stage and treatment, and ECOG performance scale at enrollment [49] will be abstracted from EMR.

#### Implementation outcomes

3.11.4

Implementation outcomes for patients in the FinEd arm include patients' report of use of resources received in FinEd arm, and their perception of comprehensibility, and helpfulness of these resources measured via follow-up surveys. We will further assess patients' experience with FinEd resources through semi-structured one-on-one qualitative interviews. The interview evaluation will be guided by the Reach, Effectiveness, Adoption, Implementation, and Maintenance (RE-AIM) framework [50] to assess the intervention's overall impact and effectiveness prior to larger-scale evaluation. For patients in CostCOM arm, we will assess patients' satisfaction with the financial counseling session using follow-up surveys.

### Statistical analysis

3.12

#### Power calculation and sample size

3.12.1

This is a 3-arm pilot randomized controlled trial to gather preliminary data to plan for a large future trial. A sample size of 90 patients (30 patients in each arm) is feasible given the limits of the study timeline and will allow us to characterize key patient variables.

Power analysis was performed to estimate a one-sided 85%, 90% and 95% upper-limit confidence intervals for proportion of patient-reported cost-related cancer care nonadherence at 6 months post-randomization in an experimental arm via the Exact (Clopper-Pearson) formula when the evaluable sample size for a study arm is 30 (Table 2). With an evaluable sample size of 30 in an experimental arm and the anticipated proportion is 0.05, the estimated 95% upper-limit confidence limit is 0.17.

**Table 2 tbl2:** Estimation of one-sided upper-limit confidence interval for primary outcome via the Clopper-Pearson Exact method when the evaluable sample size of 30 in an experimental arm.

The proportion of patient-reported cost-related cancer care nonadherence at 6 months post-randomization in an experimental arm (P)	One-sided upper limit of a confidence interval via the Clopper-Pearson Exact method		
	85%	90%	95%
0.05	0.1296	0.14613	0.17251
0.1	0.19052	0.2093	0.2386
0.15	0.24806	0.26832	0.29948

SPIRIT 2025 checklist of items to address in a randomized trial protocol^a^			
Section/Topic	No	SPIRIT 2025 checklist item description	Reported on page no.
**Administrative information**			
Title and structured summary	1a	Title stating the trial design, population, and interventions, with identification as a protocol	1
	1b	Structured summary of trial design and methods, including items from the World Health Organization Trial Registration Data Set	NA
Protocol version	2	Version date and identifier	NA
Roles and responsibilities	3a	Names, affiliations, and roles of protocol contributors	1
	3b	Name and contact information for the trial sponsor	16
	3c	Role of trial sponsor and funders in design, conduct, analysis, and reporting of trial; including any authority over these activities	16
	3d	Composition, roles, and responsibilities of the coordinating site, steering committee, endpoint adjudication committee, data management team, and other individuals or groups overseeing the trial, if applicable	NA
**Open science**			
Trial registration	4	Name of trial registry, identifying number (with URL), and date of registration. If not yet registered, name of intended registry	3
Protocol and statistical analysis plan	5	Where the trial protocol and statistical analysis plan can be accessed	NA
Data sharing	6	Where and how the individual de-identified participant data (including data dictionary), statistical code, and any other materials will be accessible	16
Funding and conflicts of interest	7a	Sources of funding and other support (e.g., supply of drugs)	16
	7b	Financial and other conflicts of interest for principal investigators and steering committee members	17
Dissemination policy	8	Plans to communicate trial results to participants, healthcare professionals, the public, and other relevant groups (e.g., reporting in trial registry, plain language summary, publication)	NA
**Introduction**			
Background and rationale	9a	Scientific background and rationale, including summary of relevant studies (published and unpublished) examining benefits and harms for each intervention	4
	9b	Explanation for choice of comparator	4-5
Objectives	10	Specific objectives related to benefits and harms	5
**Methods: Patient and public involvement, trial design**			
Patient and public involvement	11	Details of, or plans for, patient or public involvement in the design, conduct, and reporting of the trial	NA
Trial design	12	Description of trial design including type of trial (e.g., parallel group, crossover), allocation ratio, and framework (e.g., superiority, equivalence, non-inferiority, exploratory)	5
**Methods: Participants, interventions, and outcomes**			
Trial setting	13	Settings (e.g., community, hospital) and locations (e.g., countries, sites) where the trial will be conducted	5
Eligibility criteria	14a	Eligibility criteria for participants	6
	14b	If applicable, eligibility criteria for sites and for individuals who will deliver the interventions (e.g., surgeons, physiotherapists)	NA
Intervention and comparator	15a	Intervention and comparator with sufficient details to allow replication including how, when, and by whom they will be administered. If relevant, where additional materials describing the intervention and comparator (e.g., intervention manual) can be accessed	6-11
	15b	Criteria for discontinuing or modifying allocated intervention/comparator for a trial participant (e.g., drug dose change in response to harms, participant request, or improving/worsening disease)	NA
	15c	Strategies to improve adherence to intervention/comparator protocols, if applicable, and any procedures for monitoring adherence (e.g., drug tablet return, sessions attended)	NA
	15d	Concomitant care that is permitted or prohibited during the trial	8
Outcomes	16	Primary and secondary outcomes, including the specific measurement variable (e.g., systolic blood pressure), analysis metric (e.g., change from baseline, final value, time to event), method of aggregation (e.g., median, proportion), and time point for each outcome	11-12
Harms	17	How harms are defined and will be assessed (e.g., systematically, non-systematically)	NA
Participant timeline	18	Time schedule of enrollment, interventions (including any run-ins and washouts), assessments, and visits for participants. A schematic diagram is highly recommended (see Figure)	6-12
Sample size	19	How sample size was determined, including all assumptions supporting the sample size calculation	13
Recruitment	20	Strategies for achieving adequate participant enrollment to reach target sample size	6
**Methods: Assignment of interventions**			
Randomization:			
Sequence generation	21a	Who will generate the random allocation sequence and the method used	8
	21b	Type of randomization (simple or restricted) and details of any factors for stratification. To reduce predictability of a random sequence, other details of any planned restriction (e.g., blocking) should be provided in a separate document that is unavailable to those who enroll participants or assign interventions	8
Allocation concealment mechanism	22	Mechanism used to implement the random allocation sequence (e.g., central computer/telephone; sequentially numbered, opaque, sealed containers), describing any steps to conceal the sequence until interventions are assigned	8
Implementation	23	Whether the personnel who will enroll and those who will assign participants to the interventions will have access to the random allocation sequence	NA
Blinding	24a	Who will be blinded after assignment to interventions (e.g., participants, care providers, outcome assessors, data analysts)	5
	24b	If blinded, how blinding will be achieved and description of the similarity of interventions	NA
	24c	If blinded, circumstances under which unblinding is permissible, and procedure for revealing a participant's allocated intervention during the trial	NA
**Methods: Data collection, management, and analysis**			
Data collection methods	25a	Plans for assessment and collection of trial data, including any related processes to promote data quality (e.g., duplicate measurements, training of assessors) and a description of trial instruments (e.g., questionnaires, laboratory tests) along with their reliability and validity, if known. Reference to where data collection forms can be accessed, if not in the protocol	7-11
	25b	Plans to promote participant retention and complete follow-up, including list of any outcome data to be collected for participants who discontinue or deviate from intervention protocols	10
Data management	26	Plans for data entry, coding, security, and storage, including any related processes to promote data quality (e.g., double data entry; range checks for data values). Reference to where details of data management procedures can be accessed, if not in the protocol	11-12
Statistical methods	27a	Statistical methods used to compare groups for primary and secondary outcomes, including harms	14
	27b	Definition of who will be included in each analysis (e.g., all randomized participants), and in which group	14
	27c	How missing data will be handled in the analysis	13
	27d	Methods for any additional analyses (e.g., subgroup and sensitivity analyses)	NA
